#### Statistical analysis

We plan to examine treatment group differences and differential group changes from baseline to follow-up for outcome measures in all 3 hypotheses using multilevel modeling [91, 92] to account for any cluster sampling effects. Hypothesized mediating effects of sleep improvement on the relationship between treatment condition and outcomes will be assessed using bootstrap confidence intervals [93]. Any recruitment bias between consenters and refusers *after* diagnostic screening, and any differential attrition effects by comparing baseline characteristics of drop-outs and continuing participants, will be investigated using these models.

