### Randomisation and blinding

After all Phase 1 assessments had been conducted (i.e., the interview and questionnaires, sleep and cardiovascular assessments), eligible participants who consented to participate in the intervention stage of the trial were randomly allocated to receive either the sleep intervention (Sleep SENSE) or the active control group (Study SENSE). A blinded statistician randomised the eligible participants stratified by gender, age and type of anxiety disorder at baseline using a minimisation method available in the MINIM program (SJW E, SJ D, P R. MINIM: minimisation programme for allocating patients to treatment in clinical trials. Unpublished document Department of Clinical Epidemiology, The London Hospital Medical College, London. 1990.) Participants and their guardians were made aware of the content of the group sessions (i.e., study skills vs. sleep skills) but not of the status of each group (i.e., intervention versus control) or the expected outcome of the study. Researchers conducting the post-intervention interviews were also blinded to which group participants had completed.

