### Sample size requirements and power calculation

A power analysis was conducted prior to commencement of the study in order to provide a guide to sample size requirements. Recruitment was school-based using a cluster sampling scheme to optimize the two-gate screening method being employed (remembering, however, that the RCT is not *cluster-based,* because allocation is at the individual level). Calculations were based on feasible differences in treatment effect at follow-up, where attrition will be greatest. We initially estimated power under assumptions of simple random sampling, and then adjustment was made for the design effect exceeding 1 due to the cluster sampling design.

The treatment effect was estimated to result in group differences of 0.45 SDs for continuous outcome measures and an odds ratio of 2.5 for case level depression, based on preliminary published findings [89]. For α = .05, 120 participants *at follow-up* was estimated to provide 80 % power. Pre-post changes due to intervention in the pilot data were significantly larger than these conservative effect size estimates [48].

Based on our previous experience, we conservatively estimated 10 % attrition from baseline to follow-up, implying that 120/0.90 = 134 adolescents would need to be randomly allocated into the two arms of the study (this was close to the 144 individuals actually randomized). We expected 60 % screening agreement, and 16 % to meet screening cut-off criteria (this was also close to the 27 % who actually met screening criteria). It was conservatively estimated that (i) 70 % meeting screening criteria would also meet diagnostic interview criteria (86 % actually did), and (ii) 50 % meeting diagnostic inclusion would participate in the RCT (65 % actually did). The estimated design effect [90] was 1.44 based on an average cluster-size of 9.275, a coefficient of variation for cluster size of 0.25, and an intra-class correlation of 0.05 on continuous outcome measures. The final estimated required sample size at baseline adjusted for design effect and attrition was 1.44 × 134 = 194 adolescents, which corresponded to estimating need to screen at 194/9.275 = 21 schools. The final actual number of schools screened was 23.

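### If the planned change-from-baseline contrast is fitted as an ordinary group-by-time term, it is less precise than a baseline-adjusted estimate that needs no new data

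*Protocol article*

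**What the plan says.** The Statistical analysis section states two targets in one sentence: "We plan to examine treatment group differences and differential group changes from baseline to follow-up". They apply to the outcomes of three hypotheses and are to be estimated by multilevel modelling, whose stated purpose is to handle cluster sampling. The section gives no model equation and no list of fixed effects. It does not say which of the two targets carries the inference.

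Under Randomisation and blinding, allocation was "stratified by gender, age and type of anxiety disorder at baseline using a minimisation method available in the MINIM program". The analysis section does not mention these three factors.

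The sample size section sets up a comparison at follow-up: "Calculations were based on feasible differences in treatment effect at follow-up, where attrition will be greatest". The continuous effect is "group differences of 0.45 SDs for continuous outcome measures".

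Table 1 shows that the anxiety, depressive-symptom and sleep-quality questionnaires are repeated at post-intervention, at the boosters and at two years. The cardiovascular and saliva measures are taken only before the intervention and at two years.

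**The concern.** A difference between arms in change from baseline is usually fitted as a group-by-time interaction, with each arm's baseline mean estimated freely. With two waves and complete data, that estimate is the difference in mean change scores. It carries the full baseline noise of both arms, although randomisation already makes the expected baseline difference zero. Conditioning on baseline, or constraining the two baseline means to be equal, targets the same treatment effect with smaller variance whenever r is below 1.

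Minimisation raises a related point. Balancing on prognostic factors reduces the true sampling variability of the treatment difference. A model that omits them does not credit that reduction, so its standard error is too large.

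What is at stake is power, not bias. There is little to spare: the sample size section calculates a need for 194 at baseline, 144 were randomised, and Trial status reports 118 eligible participants who completed the interventions and the pre/post assessments.

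**Working it through.** **The plan's own figure.** Inputs from the sample size section: effect 0.45 SD, alpha 0.05, 120 at follow-up (60 per arm, 1:1 assumed), and 80% power. Sidedness is not stated. By the normal approximation, power = Φ(0.45 × √(60/2) − z), and 0.45 × √30 = 2.465.
- One-sided: Φ(2.465 − 1.645) = 79.4%, which reproduces the stated 80%.
- Two-sided: Φ(2.465 − 1.960) = 69.3%, which does not.
- Two-sided with baseline adjustment at r = 0.48: variance factor 1 − 0.48² = 0.77 and power 80.2%, which also reproduces it.

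The stated 120 therefore fits either an unadjusted one-sided test or an adjusted two-sided one. It does not reveal which model was intended.

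**Change score against baseline adjustment.** Take equal SDs at both waves, standardised to 1.
- Variance factor for change: 2(1 − r).
- Variance factor with baseline adjustment: 1 − r² = (1 − r)(1 + r).
- Ratio of change to adjusted: 2/(1 + r). This exceeds 1 for every r below 1. The inverse, (1 + r)/2, was simulated at 0.66, 0.74 and 0.85 for r = 0.3, 0.5 and 0.7, against exact values of 0.65, 0.75 and 0.85.

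For power, use 118 participants (59 per arm), d = 0.45, two-sided alpha 0.05 and the noncentral t distribution with 116 degrees of freedom. The noncentrality is 0.45 × √(59/2) ÷ √(variance factor) = 2.444 ÷ √(variance factor). The values of r are assumptions.

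| r (assumed) | Change: factor, power | Adjusted: factor, power | Variance ratio 2/(1+r) |
|---|---|---|---|
| 0.3 | 1.40, 0.54 | 0.91, 0.72 | 1.54 |
| 0.4 | 1.20, 0.60 | 0.84, 0.75 | 1.43 |
| 0.5 | 1.00, 0.68 | 0.75, 0.80 | 1.33 |
| 0.7 | 0.60, 0.88 | 0.51, 0.92 | 1.18 |
| 0.8 | 0.40, 0.97 | 0.36, 0.98 | 1.11 |

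A comparison of follow-up values alone has factor 1 and power 0.68. Below r = 0.5 the change contrast is weaker than the follow-up comparison on which the trial was powered; above 0.5 it is stronger. The adjusted estimate is at least as precise as either at every r.

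These figures leave out the design effect and use 118 for illustration. They show the relative cost of the contrast and do not forecast the trial's power at two years.

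**Minimisation factors.** Assume they explain R² = 0.10 of outcome variance and are well balanced. The unadjusted test statistic then has SD √0.9 instead of 1.
- Actual type I error: 2Φ(−1.96/√0.9) = 2Φ(−2.066) = 3.9%.
- Power unadjusted: Φ((2.444 − 1.96)/√0.9) = 0.695.
- Power adjusted: Φ(2.444/√0.9 − 1.96) = 0.731 by the same approximation, or 0.724 by the noncentral t.

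The gain is about 3 to 4 points.

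**The case against.** The strongest reply is that the article states no model. Covariates are neither listed nor excluded, and a condensed article commonly leaves them to a full protocol or SAP. A multilevel model of group differences and differential change could hold the baseline value and the minimisation factors. A baseline-constrained model itself reports its effect through a group-by-time term, so the wording alone cannot separate the weaker model from the stronger one. This stands. A reader might infer that the planned models contain only group, time and cluster terms, and so that the trial discards precision. The documents do not support that inference, and the stated 120 does not settle it.

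Other parts of the reply also stand:
- The section plans group differences as well as differential change.
- The equivalence with a change score is exact only for two waves with complete data. It fits the cardiovascular and saliva measures most closely, and the repeatedly measured questionnaires less so.
- At r = 0.7 or 0.8 the loss is small, and R² = 0.10 has no source in the documents.
- 118 is a count at post-intervention, not at two years.
- The argument does not reach depression onset. Eligible participants had never met criteria for major depressive disorder, so there is no baseline value and no change score.

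What survives is that the section does name a change-from-baseline contrast and names no adjustment except for clustering. A more precise estimator of the same effect uses only data already collected.

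**Conclusion.** The point holds as a conditional improvement, not as a demonstrated omission. If the stated change contrast is fitted as a group-by-time term with free baseline means, its variance exceeds that of a baseline-adjusted estimate by 54%, 33% or 18% at assumed r of 0.3, 0.5 or 0.7. The corresponding power losses are about 18, 12 and 4 points, on the illustrative basis of 59 per arm, 0.45 SD and a two-sided test. Leaving out the minimisation factors would add a modest conservative effect. Neither omission would bias the estimate or inflate false positives.

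The result applies to continuous outcomes with a baseline measurement. It is tempting to carry these power figures over to the prevention of depression, which Trial status treats as the main outcome; they do not apply there. The arithmetic is firm. Whether the actual model has this weakness cannot be known from the article.

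**What to change.** For each continuous outcome measured at baseline, state that the treatment effect is the between-arm difference at follow-up, estimated from a baseline-constrained longitudinal model or from ANCOVA on the baseline value. Keep the multilevel structure for clustering, and include gender, age and type of anxiety disorder as fixed effects.

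For depression onset, compare onset between arms with adjustment for the same three factors, as far as the number of events allows, and drop any change-from-baseline wording for this outcome.

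The cost is analysis wording only. The baseline values and minimisation factors are already collected, and Trial status says the main two-year outcomes were yet to be assessed, so at that point the choice could still be fixed before those outcomes were seen. If the full protocol or SAP already specifies this, the article's sentence needs only to be brought into line with it.

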### Intervention group sessions

Sleep SENSE builds on the work of Dahl, Bootzin and Harvey [47–51] and was successfully piloted among Australian adolescent girls, demonstrating preliminary effects on both subjective and objective measures of sleep and self-reported anxiety [48]. Sleep SENSE is a multi-component group program designed to improve sleep by addressing barriers to sleep across the sleep-wake cycle. It aims to improve sleep quality in the short term and, via sustained behavior change, the long-term, and is tailored to address the unique developmental challenges and opportunities of adolescence. Like evidence-based adult treatments for insomnia, the intervention is cognitive-behavioral in approach, incorporating sleep hygiene, stimulus control, cognitive-behavior therapy and mindfulness-based therapy, and has a specific focus on identifying barriers to change via motivational interviewing. It involves 7 weekly 90-minute group sessions supported by a range of psycho-educational materials and at-home tasks. Psychologists or psychologists in training facilitated interventions sessions. A summary of the content covered in each session is displayed in Table 2. Parents/care-givers were given information sheets about the material covered in each session to ensure the adolescent’s sleep improvement goals were integrated and supported by the family.

**Table 2 Tab2:** Session outline of the sleep intervention and active control groups

Session	Sleep Intervention Group (Sleep) SENSE Content	Control Group (Study SENSE) Content
1	Introduction: education about sleep; identifying personal sleep goals; developing motivation to change	Introduction: why good study skills and habits are important for academic success.
2	Overcoming challenges to sleep: discuss good sleep hygiene and barriers to sleep, learn stimulus control strategies; introduce mindfulness and mindfulness of the breath practice.	Personal organization, time management and the home study environment.
3	Establishing a regular sleep schedule: learn about circadian rhythms and guidelines for keeping regular sleep schedule and limiting media use at bedtime; design a personal sleep plan; mindfulness of the breath practice.	Active listening, learning, and note-taking strategies.

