### Control group sessions

Study SENSE was administered by a trained education teacher and a co-facilitator for the same duration, and in the same format as the Sleep SENSE intervention. Components of the study skills group included writing persuasive essays, referencing, note taking and public speaking (see Table 2 for a summary of the content in each session).

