### Trial status

At submission of this article, Phases 1–4 had been completed, such that 118 eligible participants in nine parallel groups have completed the interventions and pre/post assessments. One additional participant completed the SENSE Study control group because of a scoring error at the screening phase, but did not meet eligibility criteria, so will be excluded from future analyses. Two-year follow-up assessments began in June 2015 and will be completed by December 2016, as such, the main outcomes of the study (preventative effects) are yet to be assessed.

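### The stated multilevel model addresses school sampling, but clustering from group delivery, which enters the treatment contrast, is not named; any outcome with a positive group ICC would get too small a standard error

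*Protocol article*

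**What the plan says.** Statistical analysis gives the model in one sentence: group differences and changes from baseline will be examined with multilevel models "to account for any cluster sampling effects". Sample size requirements and power calculation shows what that kind of cluster is: "Recruitment was school-based using a cluster sampling scheme to optimize the two-gate screening method being employed". The same section stresses that the trial is not cluster-randomised, "because allocation is at the individual level", and derives a design effect of 1.44 from school cluster size and an ICC of 0.05.

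Delivery is described elsewhere. For Sleep SENSE, Intervention group sessions says: "It involves 7 weekly 90-minute group sessions", led by psychologists or trainees. Control group sessions says that Study SENSE was run by an education teacher with a co-facilitator "for the same duration, and in the same format as the Sleep SENSE intervention". Trial status reports "118 eligible participants in nine parallel groups have completed the interventions and pre/post assessments". Ethics, consent and permissions adds that the groups met at the University, apart from one held at a school.

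No section mentions correlation among participants treated in the same group, a group or facilitator effect, or an ICC for the intervention groups.

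**The concern.** Two kinds of cluster are present, and they act differently on the treatment comparison.

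- **School.** With individual allocation, pupils from one school can fall in either arm. A shared school effect then appears on both sides of the comparison and largely cancels.
- **Intervention group.** Members share seven sessions, facilitators and peers, and all are in the same arm. A shared group effect does not cancel. It adds to the variance of the difference between arms, and a school random effect cannot absorb it because most groups do not correspond to a school.

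The plan names and budgets for the first kind and not the second. If outcomes are correlated within groups, confidence intervals from a school-only model are too narrow and tests reject too often. A positive finding on preventing depression would then be open to that objection.

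**Working it through.** **1. The plan's own design effect.** Inputs from the sample size section: mean cluster size 9.275, coefficient of variation 0.25, ICC 0.05.

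1 + ((1 + 0.25²) × 9.275 − 1) × 0.05 = 1 + (9.855 − 1) × 0.05 = 1.443

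134 × 1.443 = 193.3, rounded up to 194; 194 / 9.275 = 20.9, or 21 schools. The stated 1.44, 194 and 21 all reproduce. The division by cluster size gives schools, so the design effect covers schools and nothing else.

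**2. Does school clustering matter for the contrast?** With 118 participants, equal arms and unit variance, the standard error of the difference without any clustering is 2 / √118 = 0.184. In a simulation with 23 schools, school ICC 0.05, no group effect, 9 groups and a school random intercept, the mean model standard error was 0.184 and the empirical SD of the estimate was 0.184. School adds essentially nothing when it crosses the arms.

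**3. Does group clustering matter?** Inputs: 118 participants (Trial status). The phrase on nine groups can mean 9 in all (118 / 9 = 13.1 each) or nine pairs (118 / 18 = 6.6 each). The group ICC is an assumption, since the documents give none; 0.05 is the plan's value for schools.

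Design effect DE = 1 + (m − 1) × ICC. Standard error ratio = √DE. Actual two-sided type I error of a test that ignores the group = 2 × (1 − Φ(1.96 / √DE)).

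| Groups | ICC | DE | SE ratio | Type I error |
|---|---|---|---|---|
| 18 | 0 | 1.00 | 1.00 | 5.0% |
| 18 | 0.02 | 1.11 | 1.05 | 6.3% |
| 18 | 0.05 | 1.28 | 1.13 | 8.3% |
| 18 | 0.10 | 1.56 | 1.25 | 11.6% |
| 9 | 0 | 1.00 | 1.00 | 5.0% |
| 9 | 0.02 | 1.24 | 1.11 | 7.9% |
| 9 | 0.05 | 1.61 | 1.27 | 12.2% |
| 9 | 0.10 | 2.21 | 1.49 | 18.8% |

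**4. Check by simulation of the school-only model.** With 4000 replicates, school ICC 0.05 and group ICC 0 / 0.02 / 0.05 / 0.10, the type I error was 5.0 / 5.8 / 8.3 / 11.9% with 18 groups and 4.9 / 7.8 / 12.8 / 19.0% with 9. A t test on group means stayed at 4.2-5.1% throughout. In a smaller simulation of 300 runs, with 9 groups and group ICC 0.05, the model reported a standard error of 0.183 against an empirical SD of 0.251. The school effect does not stand in for the group effect.

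**5. Power once the group is modelled** (118 participants, 0.45 SD, two-sided, 18 groups). With no group correlation, power is about 69% by normal approximation. Using t with 16 degrees of freedom, it is 63% at ICC 0 and 53% at ICC 0.05. So about 10 points of the fall come from the correlation and about 5 to 6 from the smaller degrees of freedom.

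**The case against.** The strongest objection is that this is a condensed article with one sentence on the model. It lists no levels and does not exclude a group term, and random-effects structure is commonly left to an analysis plan. A reader might infer that the trial's analysis omits intervention groups. The article does not establish that. It does state what the multilevel models are for, ties that to school recruitment and calculates a design effect for it. The stated purpose is therefore too narrow for the design, and that can be criticised without knowing the unseen plan.

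A reader might also infer that standard errors are too small, and type I error above 5%, for every hypothesis. The documents do not support that either. Both need a positive group ICC, none is given, and at ICC 0 the school-only model holds its level. The outcomes range from questionnaires to actigraphy, saliva markers, endothelial function and depression onset over two years. Nothing shows that seven shared sessions induce the same correlation in all of them, or that it lasts. The statement has to be made outcome by outcome.

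Three further points stand in part:

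- The highest error rates need 9 groups in total. Nine concurrent pairs is at least as natural a reading, and the text does not settle it.
- That school crosses the arms is expected from individual allocation, not guaranteed. Minimisation did not use school, and in the one group held at a school the two clusters overlap.
- It would be wrong to attribute the whole gap between the plan's 80% power and 53% to group clustering. The step from 80% to about 69% is a separate sample size matter.

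**Conclusion.** The concern holds in conditional form. The article's stated model and its design effect address schools, which should contribute little to the variance of the treatment contrast. They do not address the intervention groups, which are nested in arm. For any outcome with a positive intervention-group ICC, a school-only model understates the standard error of the treatment effect.

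For an assumed ICC of 0.02 to 0.10 and 118 participants, the true standard error is 1.05 to 1.25 times the reported one with 18 groups and 1.11 to 1.49 times with 9. The two-sided type I error is about 6-12% and 8-19% respectively. These figures rest on the assumed ICC, groups of equal size and equal arms. They say nothing about which outcomes are affected.

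The article reports that the two-year outcomes had not yet been assessed, so the model could still be fixed before those results were known.

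**What to change.** In Statistical analysis, state that:

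- the models for all outcomes include a random effect for intervention group nested within arm, in addition to school;
- continuous outcomes use Kenward-Roger or Satterthwaite degrees of freedom, and depression onset an equivalent small-sample approach;
- the intervention-group ICC is reported for each outcome.

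Cohort fixed effects and arm-specific group variances should be optional, used only if estimable. With 9 groups in all they may not be, and with nine pairs a fixed cohort effect leaves about 8 degrees of freedom for the arm contrast.

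State how randomised participants who never attended a group are handled. Randomisation and blinding describes allocation to an arm, not to a particular group, and 144 were randomised against 118 who completed the interventions and pre/post assessments. One workable rule is to use the scheduled group where it was recorded and otherwise to treat the participant as a singleton. In Trial status, say whether there were 9 or 18 groups.

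The cost is analysis wording and retrieval of group membership, with no new assessments. Intervals become somewhat wider and power lower. If an unseen analysis plan already includes a group term, it is enough to confirm this and align the article's wording with it.
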